**Methods:**

This will be a pragmatic, single-center, open, controlled, 2-arm parallel-group superiority randomized trial comparing mobile app and in-person follow-up care over the first month following surgery. The patient population will comprise all postoperative ambulatory surgery patients at WCH undergoing breast reconstruction. The intervention consists of a postoperative mobile app follow-up care using the quality of recovery-9 (QoR9) and a pain visual analog scale (VAS), surgery-specific questions, and surgical site photos submitted daily for the first 2 weeks and weekly for the following 2 weeks. The primary outcome is the total number of physician visits related to the surgery over the first 30-days postoperative. The secondary outcomes include (1) the total number of phone calls and emails to a health care professional related to surgery, (2) complication rate, (3) societal and health care system costs, and (4) patient satisfaction over the first 30 days postoperative. Permutated-block randomization will be conducted by blocks of 4-6 using the program ralloc in Stata. This is an open study due to the nature of the intervention.

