## Methods

### Design Overview

This will be a pragmatic, single-center, open, controlled, 2-arm parallel-group superiority randomized trial comparing mobile app and in-person follow-up care over the first 30 days following surgery. Permutated-block randomization will be conducted by blocks of 4-6 using the program ralloc in Stata statistical software [20].

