### Intervention

Eligible patients will be randomized in equal proportions (1:1) between mobile app and in-person follow-up care. All patients will receive what is currently the medical standard of care in this hospital. Patients in the conventional follow-up group will have a planned clinic follow-up at 4 weeks postoperative. This is the follow-up schedule currently used by both surgeons. At these scheduled follow-ups, patients will be asked to complete the VAS to assess pain and the QoR-9.

The mobile app follow-up group will have no planned in-person follow-up at 1 week and 4 weeks postoperative. However, these visits will be replaced with surgical site examination via submitted photos, VAS, and QoR-9 questionnaire monitoring. All of this information is submitted via the mobile app (QoC Health Inc, Toronto). Patient reporting will begin following discharge from the recovery room. Since 75% of complications occur within the first 2 weeks of discharge [21], we will use daily monitoring for 2 weeks and then weekly monitoring for 4 weeks. The data entered through the mobile phone app will reach a double-encrypted server. The surgeon will then use a wireless interface to access that data and monitor the patient’s condition (not in real time). High pain scores will be flagged in the database for quick viewing. Any red flags will prompt in-person follow-up. Physicians will summarize the clinical findings recorded by the mobile app at 1 week and 4 weeks postoperative using the prototypical subjective, objective, assessment, and plan (SOAP) note.

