### Primary Outcome

The total number of physician visits (including specialist, family physician, and emergency department) related to the surgery. These data will be captured at 4 weeks after surgery.

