### Secondary Outcomes

The total number of health care telephone calls and emails (including specialist, family physician, and emergency department) related to the surgery will be captured at 4 weeks after surgery.

We will also record and report all complications occurring within the 30-day period. This was chosen based on literature surrounding postoperative complications in the first 30 days [21]. This will be captured at 4 weeks after surgery. The complication rate within this patient population is 4%, with 1% rate of reoperation. The most common complications are superficial skin infections managed with a short course of oral antibiotics. In the pilot study, all (1/30) superficial skin infections were picked up by the mobile phone app and antibiotic prescriptions were called in to the patient’s local pharmacy [6]. Rare non-serious complications include seromas and wound dehiscence. All wound dehiscence (1/30) were picked up by the app in the pilot study. These both warrant a trial of conservative (watch-and-wait) therapy. After failed conservative therapy, seroma may be drained via ultrasound guided needle aspiration. Wound dehiscence may require surgical management under local anesthetic in the clinic or, if more involved, under regional anesthetic in the operating room. Rare and potentially serious complications include hematomas. If a hematoma is small and non-expanding, it can be managed conservatively (watch-and-wait). If it is larger and expanding, it may require urgent (<24 hours) evacuation in the operating room. This type of urgent situation presents to the emergency department, not to a clinic visit.

There is no potential for clinical compromise in the telemedicine group. If anything, superficial skin infections may be identified and treated earlier. Any study participant can schedule a face-to-face postoperative visit with the surgeon at any time; however it is anticipated that the mobile phone follow-up care will eliminate the need for one or more clinic visits. Devices may be returned to the clinic in-person or by standard mail.

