### Data Collection Overview

The QoR and VAS pain scores will be collected from all patients at 4 weeks after surgery (see Figure 1). The in-person study group will perform this via telephone interview, and the mobile app group will perform this via mobile app. Our study coordination or researchers (KA) will collect all telephone questionnaires at 4 weeks after surgery. These persons will administer the questionnaire capturing email, telephone and in-person encounters, postoperative complications (Multimedia Appendix 3), and the cost survey (Multimedia Appendix 4). They will also administer the post-pilot survey capturing patient satisfaction (Multimedia Appendix 1) at 4 weeks after surgery. The study coordinator or researcher (KA) will attempt to contact every patient four times over the 4^th^ week after surgery.

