### Measuring Outcome Variables

#### Primary Outcome

The total number of physician visits (including specialist, family physician, and emergency department) related to the surgery will be captured at 4 weeks after surgery by the study coordinator over telephone (see Multimedia Appendix 3).

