## Appendix

Multimedia Appendix 1 Post-pilot satisfaction survey capturing patient satisfaction with care and information provided for all patients, to be completed by all patients at week four.

Multimedia Appendix 2 QoR9 and Pain VAS.

Multimedia Appendix 3 Telephone questionnaire capturing email, telephone and in-person encounters and postoperative complications. All patients will complete this at week four.

Multimedia Appendix 4 Telephone questionnaire capturing patient costs, to be completed by all patients at week two and week four.

Multimedia Appendix 5 CIHR reviewer comments.

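### The visit count covers 30 days, but the only interview that records it is attempted in week 4, so days 29-30 go unobserved and a control patient's planned 4-week visit can be missed

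*Protocol article*

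**What the plan says.** **Window.** The Abstract states: "The primary outcome is the total number of physician visits related to the surgery over the first 30-days postoperative". Design Overview describes the trial as "comparing mobile app and in-person follow-up care over the first 30 days following surgery". For complications, Secondary Outcomes says: "We will also record and report all complications occurring within the 30-day period". Net Benefit Regression uses the same 30 days for both cost and effect.

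**Capture.** Primary Outcome says of the visit count: "These data will be captured at 4 weeks after surgery". Measuring Outcome Variables adds that it "will be captured at 4 weeks after surgery by the study coordinator over telephone". Data Collection Overview says the study coordinator or researcher "will attempt to contact every patient four times over the 4^th^ week after surgery". The Appendix list says of the encounter and complication questionnaire: "All patients will complete this at week four". No later call is described, and no count of visits from clinic records.

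**Planned visits.** Intervention states: "Patients in the conventional follow-up group will have a planned clinic follow-up at 4 weeks postoperative". The same section gives the app arm no planned in-person visit at 1 or 4 weeks. Sample Size assumes an average of two visits in the first month under usual care, with at least one averted by the app.

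**The concern.** The recording window closes before the outcome window does, and at about the time of a visit that only one arm has scheduled. A control patient who answers the first call of the week may not yet have attended. She would be entered as a complete case with one visit too few. No matching planned visit can be lost in the app arm.

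The planned effect is one visit, so each missed 4-week visit removes, for that patient, the whole difference the trial is sized to detect. A complication first noticed at that visit would go unrecorded, and so would the visit's travel, time and clinic costs. Both feed the net benefit regression.

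Analysis cannot repair this. A shortened interview does not look like missing data, so the best-case and worst-case scenarios under Handling Missing Data would not pick it up. How much is lost would depend on how quickly each patient answers the telephone.

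**Working it through.** **1. Calendar.** Counting the day of surgery as day 0, the 4th week is days 22-28.
- Last attempt: day 28 at the latest. Unobserved: 30 − 28 = 2 days, in both arms.
- Control visit: nominally day 28. A patient reached on day 22 is interviewed 28 − 22 = 6 days before it.

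**2. The plan's own sample size.** Inputs from Sample Size: means 2 and 1, 32 per group, 95% power, P=.05 (sidedness not stated), 10% dropout.

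For arm totals k1 and k2 with n per arm, the E-test statistic is T = (k1 − k2)/√(k1 + k2). Its p-value is computed with both totals Poisson with mean (k1 + k2)/2. Power is the sum, over all (k1, k2) with p ≤ 0.05, of the product of the Poisson probabilities with means n·λ1 and n·λ2.
- One-sided 0.05: n = 31 gives 94.7% and n = 32 gives 95.2%, so the minimum is 32. This matches the plan.
- Two-sided 0.05: n = 32 gives 91.1%; 95% needs 39 per group.
- Dropout: 32/0.9 = 35.6, rounded up to 36. This matches.

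Both versions are carried forward because the plan does not state the side.

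**3. Effect of missed visits.** Let m be the share of control 4-week visits not yet made at the time of the call. The documents give no value, so m is an assumption. Taking one 4-week visit per control patient and no loss in the app arm, the recorded means are 2 − m and 1, and the recorded difference is 1 − m.

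| m (assumed) | Recorded means | Difference | Power at 32 per group, one-sided / two-sided |
|---|---|---|---|
| 0 | 2.00 vs 1 | 1.00 | 95.2% / 91.1% |
| 25% | 1.75 vs 1 | 0.75 | 82.4% / 73.1% |
| 50% | 1.50 vs 1 | 0.50 | 55.9% / 43.2% |
| 75% | 1.25 vs 1 | 0.25 | 24.1% / 15.4% |

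To hold 95% power, the number per group would have to be 52 (one-sided) or 63 (two-sided) at m = 25%, and 108 or 129 at m = 50%.

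The final analysis is a Poisson regression. The E-test is used here because the plan sized the trial with it.

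**4. Direction.** Fewer recorded control visits shrink the difference. The error therefore works against the app and costs power.

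**The case against.** The strongest reply is that the order of call and visit is not fixed. Most of the text places capture at 4 weeks, the same nominal time as the control visit, and only the sentence on contact attempts spreads the calls across a week. The clinic visit has no stated window and may fall before the call. The data collection figure and the encounter questionnaire are not shown, and either might settle the order. This stands as a limit. A reader might infer that the 4-week visit is always missed, or that the planned difference vanishes. The documents support only that the visit can be missed. But nothing shown requires the call to follow the visit, and even a day-28 call leaves days 29-30 unrecorded.

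A reader might also infer that only the control arm loses data. That goes too far. App patients may ask for a visit at any time, red flags prompt one, and their week-4 review could lead to a visit after the call. The loss is probably unequal, because only controls have a visit planned then, but it is not confined to them.

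Nor can costs be said to be captured only once. The Appendix lists the cost survey at weeks two and four, although Measuring Outcome Variables mentions only 4 weeks. A week-two survey would still not record the costs of a 4-week visit.

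Finally, the error cannot manufacture superiority on the visit count. That is right, and it limits the harm to a diluted estimate and a greater risk of a false negative.

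**Conclusion.** The point holds in this form: the recording window is shorter than the outcome window, and it can close before a visit planned in the control arm alone. The two-day gap follows directly from the text and affects both arms. The unequal loss is probable rather than certain, and it biases the visit difference towards no effect.

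The size is conditional. If a quarter of control 4-week visits were missed, power at 32 per group would fall from 95% to 82% one-sided, or from 91% to 73% two-sided. If half were missed, it would fall to 56% or 43%. These figures rest on the plan's 2 versus 1 visits, one 4-week visit per control patient, no loss in the app arm, and shares that no document supplies.

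The control schedule is itself unsettled. Intervention names a single planned control visit, at 4 weeks, yet says the visits replaced in the app arm are those at 1 and 4 weeks, and Sample Size assumes two visits. The calculation takes the two-visit assumption as given.

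**What to change.** In both arms, start the interview attempts after day 30, for example on days 31-37. Ask about visits, calls and emails, complications and costs from surgery through day 30. Take visits to the study hospital for days 0-30 from its own clinic records, and use the interview for visits elsewhere. The trial has a single center, so one hospital's records suffice.

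The cost is about one extra week per patient, slightly longer recall and a look-up of existing records. The sample size need not change on this account.

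Intervention and Sample Size should also be reconciled on the number and timing of planned control visits, and the cost survey's timing should be stated the same way in the text and the Appendix.

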**Figure 1 figure1:**
[figure not shown]
Data collection overview diagram.

### Measuring Outcome Variables

#### Primary Outcome

The total number of physician visits (including specialist, family physician, and emergency department) related to the surgery will be captured at 4 weeks after surgery by the study coordinator over telephone (see Multimedia Appendix 3).

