### Recruitment Procedures

All patients presenting for breast reconstruction will be screened for inclusion in the study. We will consecutively approach patients to participate in the study. A member of the health care team will inform patients about the study prior to surgery. If interested in participating, a study coordinator or researcher (KA) will introduce the patient to the technology so that they can better judge what is required of them. This will include introduction to the QoR-9 and VAS score on the mobile app (see Multimedia Appendix 2). The patients will be assured of their ongoing surgical care regardless of their participation. Patients who agree to participate will review and sign the appropriate consent form. They will have the opportunity to discuss the study with the attending surgeon. Written consent will be obtained for all prospective patients. After the patient has consented to the trial, they will be randomized to the mobile app or in-person follow-up arm using the program ralloc in Stata statistical software [20].

The mobile app follow-up care stream will receive an instruction sheet detailing how to use the app. The patient will receive training on how to use the app from the study coordinator or researcher (KA). The patient will be given a mobile phone on the day of surgery and will review the use of the mobile app again at this time. This will also help the patient judge what is required of them and serve as an opt-out point.

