####  Allocation Concealment

As potential subjects are identified, a research assistant will be notified to assess eligibility. Once a subject is deemed eligible for enrollment, has given the necessary informed consent, has been enrolled, and has had her demographic information abstracted from her clinic records, the research assistant will issue the next in a series of sequentially numbered, sealed, opaque envelopes containing group assignment. The participant’s clinic number will be written on the envelope, and the participant will be required to open and read the treatment assignment in the presence of the research assistant, who will then enter the group assignment into a database and store the envelope. If a participant is unable to read, the research assistant will read the group assignment on her behalf.

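### The primary visit count rests only on a week-4 telephone self-report taken by unblinded staff, with no check against the hospital's own records

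*Protocol article*

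**What the plan says.** The protocol article defines the primary outcome as "The total number of physician visits (including specialist, family physician, and emergency department) related to the surgery". The abstract sets the period at the first 30 days after surgery. Under Measuring Outcome Variables the count "will be captured at 4 weeks after surgery by the study coordinator over telephone", and the Appendix list describes the instrument as a "Telephone questionnaire capturing email, telephone and in-person encounters and postoperative complications", completed by all patients at week four. No second source is named.

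Under Data Collection Overview, the study coordinator or a researcher makes the calls and "will attempt to contact every patient four times" during the fourth week. Under Recruitment Procedures, "The patient will receive training on how to use the app from the study coordinator or researcher". The abstract states: "This is an open study due to the nature of the intervention". No blinded assessor is described, and the coordinator also receives the allocation envelopes (Implementation of Randomization Procedures).

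Clinic records are within the study's reach. Under Allocation Concealment, a participant is randomized only once she "has had her demographic information abstracted from her clinic records". Research Study Data Storage notes that physicians keep patient charts. The Limitations section treats self-report as a weakness for travel time and costs, and plans a postal-code cross-check there. It says nothing similar about the visit count.

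**The concern.** Two kinds of error could enter the primary comparison.

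The first is reporting that differs by arm. Patients know their allocation, and so do the callers. Callers belong to the same small group that introduces and teaches the app. Patients may forget visits, or leave some out as not counting, to a different extent in each arm. With one or two visits expected per patient, a small reporting difference is a large fraction of the count.

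The second is timing. The call falls in week 4, the outcome runs to day 30, and the control arm has a planned clinic visit at 4 weeks that the app arm does not have. A call made before that visit misses it in controls only.

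The planned surgeon visit is the component that the intervention is meant to avert. It is also the component that the hospital's own records should be able to confirm. As written, a cost input gets a cross-check and the primary outcome gets none.

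**Working it through.** **The plan's own figure.** Inputs from Sample Size: control mean 2 visits, app mean 1, 32 per group, P=.05, power 95%, 10% dropout. The exact power of the E-test for two Poisson means at 32 per group is 95.2% one-sided and 91.1% two-sided. The stated figure is therefore reproduced as a one-sided test; the article does not give the sidedness, which is a separate matter. Dropout: 32/0.9 = 35.6, rounded up to 36, as stated. The scenarios below use the two-sided test at 32 per group, so the reference power is 91.1%.

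**Differential reporting.** If the arms report fractions r(app) and r(control) of their true visits, then

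observed ratio = (app mean × r(app)) / (control mean × r(control)).

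The documents give no reporting rates, so every r here is an assumption.

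- App patients report 90% or 80% as completely as controls: 0.50 × 0.90 = 0.45; 0.50 × 0.80 = 0.40.
- Controls report 90% or 80%, app patients all: 1/(2 × 0.90) = 0.56; 1/(2 × 0.80) = 0.63.

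| Assumed reporting fraction | True means 2 vs 2, one arm under-reports: rejection rate | True means 2 vs 1, controls only under-report: power | True means 2 vs 1, both arms under-report: power |
|---|---|---|---|
| 100% | 4.9% | 91.1% | 91.1% |
| 95% | 5.9% | 85.6% | 89.7% |
| 90% | 8.8% | 77.8% | 88.0% |
| 80% | 22.0% | 56.0% | 84.0% |

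Under-reporting that is equal in both arms costs little. Under-reporting in one arm costs much more.

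**Timing.** Let m be the share of planned 4-week control visits that come after the call; m is also an assumption. The observed control mean is 2 − m.

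- m = 0.25: control mean 1.75, ratio 1/1.75 = 0.57. Power lies between the results for control means of 1.8 (77.8%) and 1.6 (56.0%).
- m = 0.50: control mean 1.50, ratio 1/1.50 = 0.67. Power lies between the results for 1.6 (56.0%) and 1.4 (30.7%).

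This error works against the app.

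**Unreached patients.** The dropout allowance is 36 − 32 = 4 per arm. Handling Missing Data plans best and worst cases without giving the extremes; 0 and 4 visits are assumed here.

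- Observed: 64 vs 32 visits, ratio 0.50. z = ln(0.50)/√(1/64 + 1/32) = −0.693/0.217 = −3.20, p about 0.001.
- Worst case (control 0 each, app 4 each): 64 vs 32 + 16 = 48, ratio 0.75. z = ln(0.75)/√(1/64 + 1/48) = −0.288/0.191 = −1.51, p about 0.13.
- Best case: 64 + 16 = 80 vs 32, ratio 0.40.

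For an unreached patient, records would supply the hospital visits. Only visits elsewhere would then have to be set to an extreme, so the range narrows by an amount that depends on the unknown share of outside visits.

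**The case against.** The present method has a real virtue: the same questionnaire, at the same time, in both arms. Recall covers only about four weeks and one or two visits, often involving long travel, so omissions may be few. If the planned effect is real, app-arm omission of 10-20% lowers the app mean by 0.1-0.2 visits against a standard error of √(3/32) = 0.31, and the conclusion stands. This is correct. The harm is greatest when the true difference is small or absent, or when controls are the arm that under-reports.

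Mixing sources may also create an imbalance. If app patients make more of their visits elsewhere, records would make the control count more complete. Applying both sources identically in both arms, and still asking everyone about outside visits, meets most of this. Some residue stays, because outside visits remain on recall.

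The questionnaire and the data-collection figure are not shown, and a full protocol might add source verification. But the article does not leave the source open: it names the telephone call.

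Three stronger readings are tempting and not supported.

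- A reader might infer that the person who trained each app patient also interviews her. The article assigns both tasks to the coordinator or a researcher, so the role is shared but the person need not be. Perceived Undue Influence adds that neither takes part in direct care.
- A reader might infer that records would largely remove missing outcomes. The outcome includes family physician and emergency visits, patients come from across Ontario, and records here hold only this hospital's part.
- A reader might infer that the bias favours the app. Nothing in the article fixes its direction, and the timing error runs the other way.

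That charts show attended clinic visits is itself an inference from the two mentions of records, though a safe one.

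**Conclusion.** The concern holds in a limited form. In an open trial the primary count comes from one unverified telephone self-report, taken in week 4 by staff in the same roles that train the app arm. The component the intervention targets could be checked at the single study hospital. The size of any bias cannot be derived from the article, and its direction is unknown; the calculations show sensitivity and are not estimates. A one-arm shortfall of 10-20% is enough to raise the false-positive rate from 4.9% to 8.8-22.0%, or to cut power from 91.1% to 77.8-56.0%. The timing gap is more concrete, since it follows from the article's own schedule and can affect only controls, but how often a call would precede the visit is not stated. These results assume Poisson counts, means of 2 and 1, 32 per group and a two-sided test. The change is worth making because it is cheap and protects the primary outcome directly.

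**What to change.** For every randomized patient in both arms, extract visits to the hospital's surgeons and clinic over days 0-30 from scheduling and chart records. Let the record decide whether a hospital visit occurred. This also captures a control visit that falls after the call. Keep the telephone questionnaire in both arms for family physician, outside emergency and other outside visits. Judge whether a visit is related to the surgery by the same rule in both arms, since a scheduling entry may not settle that. For unreached patients, enter the recorded hospital visits and apply the best and worst cases only to the outside component.

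The outcome definition and the sample size stay as they are. The cost is a brief chart check for 72 patients by existing staff, and possibly a consent sentence on record access. Patients who withdraw may not be covered.
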